# Acupuncture effect on dumping syndrome in esophagus cancer patients with feeding jejunostomy: A study protocol for a single blind randomized control trial

**DOI:** 10.1097/MD.0000000000033895

**Published:** 2023-06-09

**Keywords:** acupuncture, digestion, dumping syndrome, esophagus cancer, feeding jejunostomy, malnourishment, weight loss

## Abstract

**Methods::**

Sixty advanced esophageal cancer patients post-feeding jejunostomy will be divided into 2 equal groups, an intervention group (n = 30) and a control group (n = 30). Patients in the intervention group will receive acupuncture using the following acupoints: ST36 (Zusanli), ST37 (Shangjuxu), ST39 (Xiajuxu), PC6 (Neiguan), LI4 (Hegu), and Liv 3 (Taichung). Patients in the control group will receive shallow acupuncture on 12 non-acupoints (sham points), 1 cm from the above mention points. Patients and assessors will be blind to trial allocation. Both groups will receive acupuncture twice a week for 6 weeks. The main outcome measurements are: body weight, BMI, Sigstad’s score, and the Arts’ dumping questionnaire.

**Discussion::**

There are no previous studies that have examined the use of acupuncture on patients with dumping syndrome. This single-blind randomized control trial will investigate the effect of acupuncture on dumping syndrome in advanced esophagus cancer patients with feeding jejunostomy. The results will determine if verum acupuncture can affect dumping syndrome and prevent weight loss.

## 1. Introduction

Esophagus cancer’s new cases in 2020 were 604,100, the 10th most common cancer in the world. Esophagus cancer also had an astonishing 544,076 new deaths in 2020, which represents 5.5 percent of all cancer mortality.^[1,2]^ Based on the current trend the forecast for the burden of esophagus cancer is expecting an increase to 739,666 new cases and 723,466 deaths in 2030, and 987,723 new cases and 914,304 deaths in 2040.^[2]^ Not long ago, the 5 years survival for esophageal cancer was 21.7% (United States data from 2011–2019).^[3]^ Esophagus cancer patients often suffer from progressive dysphagia due to the tumor and its effect on the integrity and function of the esophagus, which leads to serious weight loss and possible malnourishment.^[4]^ A study on 154 French hospital wards found that 60.2% of the patients with esophagus and/or stomach cancer were malnourished.^[5]^ In a study including 1482 esophageal cancer patients existing prevalence of malnutrition was around 50% of the patients, when measured by the NRS-2002.^[6]^ Advanced esophagus cancer patients have a limited oral feeding ability and their nutrition support is often provided through a jejunostomy tube feeding. Especially at the time of preoperative chemotherapy and radiotherapy sessions.^[7,8]^ In clinical observation of patients after jejunostomy, the presence of dumping syndrome was observed, due to the faster speed at which the food enters the intestine through the jejunostomy tube.^[9]^ The prevalence of dumping syndrome is considered high among esophagus cancer patients, with a prevalence ranging between 20-50% of the patients.^[10,11]^ Dumping syndrome is a condition in which the food is rapidly introduced into the intestine at a rate that is faster than normal, this usually occurs due to anatomical and physiological changes in the digestive system. Dumping syndrome’s main symptom is diarrhea, other symptoms contain abdominal cramps, nausea, and vasoactive symptoms like tachycardia, palpitations, fatigue, a desire to lie down following eating, pallor, diaphoresis, lightheadedness, hypotension, headache, and syncope.^[12,13]^ This often occurs 1 hour after a meal although late dumping can occur 1 to 3 hours after a meal.^[12,14]^ After the food rapidly enters the intestine a large number of hormones are secreted, such as neurostatin, vasoactive intestinal peptide, incretins, insulin, and glucagon which cause the vasomotor symptoms to appear.^[14]^ Dumping syndrome is also associated with weight loss.^[15,16]^ This is particularly important for esophagus cancer patients due to their initial high risk of malnourishment.^[5]^ The management of dumping syndrome in Western medicine is mainly based on dietary adjustments.^[16]^

Acupuncture is a treatment that was previously shown to reduce diarrhea for irritable bowel syndrome patients^[17,18]^ along with a reduction in gastroparesis syndrome.^[19,20]^ Acupuncture was also shown the ability to regulate gastrointestinal mobility through different physiological pathways.^[21]^ Acupuncture decreased the fasting glucagon-like peptide-1 levels in an animal model^[22]^ and also showed the ability to decrease insulin and glucagon levels.^[23]^ In oncological patients, acupuncture reduced chemotherapy-related abdominal pain, nausea, vomiting, and diarrhea with good safety.^[24–26]^ We have chosen to compare acupuncture to shallow needling on sham non-acupoint in order to generate a reliable placebo effect that resembles acupuncture intervention processes.

There are no previous studies that have examined the direct use of acupuncture on dumping syndrome. The goal of this single-blind randomized control trial is to investigate the effect of acupuncture on dumping syndrome in esophagus cancer patients with jejunostomy tube feeding. We hypothesize that acupuncture will be superior to sham acupuncture in regulating dumping syndrome.

## 2. Methods

### 2.1. Study design and settings

This single-blind randomized control trial will be implemented in the Department of thoracic surgery of China medical university hospital (CMUH), Taichung City, Taiwan. The study will be initiated on February 2023 and will be concluded until January 2025. This single center study will use a 1:1 ratio parallel group allocation. Informed consent will be obtained prior to the patient’s enrollment. The 2 groups are an intervention group (INT) and a control group (CON). The study was approved by the institutional review board (IRB) of CMUH (approval no. CMUH111-REC3-004) and a study protocol registration online on https://clinicaltrials.gov/ct2/show/NCT05801666 (registration no. NCT05801666). The study aims to examine the effect of acupuncture on preventing and treating dumping syndrome in esophagus cancer patients after feeding jejunostomy surgery. The study will also measure the effect of acupuncture on preventing malnutrition using body weight and body mass index (BMI) (see Fig. 1). In this study, both the patients and the assessors of outcome measurements will be blinded to the group’s allocation.

**Figure 1. F1:**
[figure not shown]
Study flow chart. The study flow chart describes the study processes. BW = body weight, BMI = body mass index, MV = mechanical ventilation, ICU = intensive care unit.

### 2.2. Participants

Sixty esophagus cancer patients after feeding jejunostomy from CMUH from the department of chest surgery will be included in this study. The patients will be randomly divided equally into 30 patients in the intervention or the control group after meeting the study’s inclusion criteria and obtaining informed consent from the patients (or a legal guardian).

### 2.3. Inclusion criteria

Age: 20 to 80-year-old

Advanced esophageal cancer

Post feeding jejunostomy

Plan of Concurrent Chemoradiation Therapy for esophageal cancer

### 2.4. Exclusion criteria

Acute infection

Unstable vital signs

Other medical conditions which would affect nutrition status

### 2.5. Recruitment strategies

During a patient’s consultation with a doctor, the doctor will inform the relevant patients about a study taking place. Study personnel will explain the pros and cons of the study in case the patient intends to enroll in the study. The study personnel will arrange meetings with the doctors in the department of thoracic surgery in order to increase the department doctor’s awareness for the study inclusion criteria.

### 2.6. Informed consent

Once a patient meets the inclusion criteria, the patient or the patient’s legal guardian will be asked for interest in joining the study. Study personnel will explain the benefits and risks of the study prior the signing informed consent. After signing the informed consent, the patient has the right to ask for study withdrawal at any time. If the patient agrees, his/her data will be still used for the study data analysis.

### 2.7. Randomization and allocation concealment

For study randomization, a 1:1 simple computer-based random number table without stratification was generated via IBM SPSS statistics version 22 (SPSS Inc, Chicago, IL). The 2 groups’ random sequentially number along with correlated acupuncture/sham points picture and name was placed inside 60 nontransparent, sealed envelopes by a study personnel [name]. At the time of intervention, a study research assistant will deliver a random envelope to the acupuncture doctor. The acupuncture doctor will attach the patient’s information to the envelope and will provide the intervention according to the acupuncture/sham points in the envelope.

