### 2.16. Statistical analysis

The statistical analysis for all measurements will analyze changes from baseline and changes over time. Categorical data will be presented as a percentage (n %), while continuous data will be presented as mean ± standard deviation. For changes from baseline the paired *t* test will be used. The independent *t* test or the Mann–Whitney *U* test will analyze continuous variables depending on applicability, and the Chi-square test or Fisher’s exact test (as appropriate) will be used for categorical variables. For repeat measurements data the repeat measures ANOVA will be used. The IBM SPSS Statistics version 22.0 (SPSS Inc, Chicago, IL) will be used for data analysis, and significance will be determined at a *P* value < .05. If applicable, a subgroup analysis will be done on tumor stage, age, BMI, dumping syndrome status at baseline and dumping syndrome type. If there are any missing data, they will be imputed using multiple imputations (if applicable).

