Limitations of the study include a specific Taiwanese population and cannot be generalized to other populations. This study is also only a single-center study. The study protocol could not apply a double-blind design due to the type of intervention (manual acupuncture). The study will investigate the role of acupuncture in the prevention of dumping syndrome and malnourishment, the study does not require a positive Sigstad’s score to verify dumping syndrome as a condition for inclusion, therefore it is possible that the number of patients that will develop dumping syndrome could be low, in this case, the study will focus on body weight and BMI as the main outcomes to assess the prevention of malnourishment. The study did not specify the cancer stage in the inclusion criteria. High mortality rates in Esophagus cancer might impair the completeness of the data and can increase the levels of missing data.

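### The between-arm tests name no term for baseline dumping, although patients with and without it are mixed and allocation is unstratified; a baseline-adjusted model would recover precision and protect against chance imbalance

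*Protocol article*

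**What the plan says.** Section 2.7 says that "a 1:1 simple computer-based random number table without stratification was generated via IBM SPSS statistics version 22" and that 60 sealed envelopes were filled from it. Section 2.2 fixes the arm sizes: "The patients will be randomly divided equally into 30 patients in the intervention or the control group".

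The limitations in section 3 say that "the study does not require a positive Sigstad’s score to verify dumping syndrome as a condition for inclusion". The introduction describes dumping in esophageal cancer "with a prevalence ranging between 20-50% of the patients"; that is a literature figure, not the trial's own baseline rate. Section 3 also warns that "it is possible that the number of patients that will develop dumping syndrome could be low".

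Section 2.12 makes the Sigstad score and the Arts questionnaire main outcomes, taken at baseline, week 3 and week 6. Section 2.16 plans analyses of change from baseline and over time: paired t tests, independent t or Mann–Whitney tests, chi-square or Fisher tests, and repeated measures ANOVA. No covariate is named. Baseline dumping appears only in a conditional plan under which "a subgroup analysis will be done on tumor stage, age, BMI, dumping syndrome status at baseline and dumping syndrome type".

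**The concern.** Whether a patient already has dumping at entry is likely to be a strong predictor of the dumping scores at weeks 3 and 6. The plan treats it as important enough for a subgroup analysis, yet uses it neither in the allocation nor in the named between-arm comparison.

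Two things are at stake. First, the trial has only one allocation. If that allocation is lopsided on baseline dumping, a test without a baseline term credits part of the gap to acupuncture or hides a true effect behind it. Second, even when the arms are balanced, variation explained by baseline dumping stays in the error term of an unadjusted follow-up test and costs power.

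**Working it through.** **The plan's own figure.** A two-sided t test with d = 0.8, alpha 0.05 and 80% power needs 25.5, so 26 per arm or 52 in total; 52 × 1.15 = 59.8, so 60. This matches the 60 in section 2.14 (its 26 fits as a per-arm number). With all 30 per arm analysed, power is 86%.

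**Chance of a gap.** Inputs: 60 patients split 30/30 (2.2), no stratification (2.7), K patients with dumping at baseline. K is not given. I assume 20–50% from the introduction, so K = 12 to 30. A gap of 20 points is 6 patients of 30. With x of the K falling in one arm,

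P = Σ C(K,x)·C(60−K,30−x)/C(60,30), summed over |2x − K| ≥ 6.

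For K = 12 this means x ≥ 9 or x ≤ 3: 2 × (0.04151 + 0.00934 + 0.00117 + 0.00006) = 0.104.

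| K | 12 | 13 | 15 | 18 | 21 | 24 | 27 | 30 |
|---|---|---|---|---|---|---|---|---|
| P(gap ≥ 20 points) | 10.4% | 5.7% | 7.2% | 15.8% | 10.3% | 18.7% | 11.9% | 19.6% |

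Odd K gives less because the smallest qualifying gap is then 7 patients. Averaged over sampling at 20%, 35% and 50% prevalence, the chance is 7.5%, 13.6% and 15.5% with 30/30, and 5.7%, 11.1% and 13.0% if allocation is an unrestricted coin toss. Hence roughly 6–20%. With rarer dumping: K = 10 gives 8.0%, K = 8 gives 5.2%, K = 6 gives 2.4%. A gap in one given direction has half these chances. With K = 12, an 8:4 or worse split has a 33% chance.

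**Effect of such a gap on an unadjusted follow-up t test.** The effect of baseline status on the week-6 score is not in the document, so it is varied (total SD 1). A gap of exactly 20 points moves the estimate by 0.20 × effect. The last two columns are simulated, given a gap of 20 points or more; power is at d = 0.8 with the gap against acupuncture.

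| Assumed effect | Shift at a 20-point gap | False-positive rate | Power |
|---|---|---|---|
| 1.5 SD | 0.30 SD | 18–26% | 34–45% |
| 1.0 SD | 0.20 SD | 10–12% | 58–61% |
| 0.75 SD | 0.15 SD | 8–9% | 67–69% |

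Over all allocations the false-positive rate is about 5% and power about 86%.

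**Do change scores remove it?** A separate null simulation assumed patients with dumping 2 SD higher at baseline and a baseline-to-follow-up correlation of 0.6. Given a gap of 20 points or more, type I error was 11–15% for the follow-up t test, about 11% for the change-score t test and 4.3–5.6% for ANCOVA on the baseline score. Over all allocations each stayed at about 5%. The change score overcorrects because of regression to the mean.

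**Gain from a model term.** Status explains b²·p(1−p) of the variance, so the standardised effect becomes 0.8/√(1 − b²p(1−p)).
- b = 0.75, p = 0.2: 0.5625 × 0.16 = 0.09; 0.8/√0.91 = 0.84; power 89%.
- b = 1.5, p = 0.2: 2.25 × 0.16 = 0.36; 0.8/√0.64 = 1.00; power about 97%.
- b = 1.5, p = 0.35: 2.25 × 0.2275 = 0.512; 0.8/√0.488 = 1.15; power 99%.

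**What stratifying adds on top.** With status in the model (b = 1.5), simulated power was 0.964 unstratified and 0.964 stratified at K = 12, and 0.991 and 0.992 at K = 21. Stratified blocks of 4 (assumed) gave a 20-point gap in 0 of 10,000 simulated allocations at each prevalence.

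**The case against.** Unstratified 1:1 allocation in a single-centre trial of 60 is a legitimate choice, openly stated. The high error rates appear only after conditioning on unlucky allocations, and power suffers only when the gap goes against acupuncture: 5.2% of allocations at K = 12 or 21, and 9.8% at K = 30. All of that stands. A reader might infer that the randomisation is faulty or the trial biased; the document does not support this.

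A reader might also infer that any imbalance passes straight into the results. It does not, because 2.16 analyses change from baseline. How far that protects depends on how much of the baseline difference persists. With a 1.5 SD effect and within-status correlation 0.5, change-score type I error in lopsided trials is about 5% if the difference persists fully, about 8% if three quarters does, and 19–25% if half vanishes. So change scores help, but are not reliable protection. The subgroup analysis does not adjust the main comparison.

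Model terms may be set out in an analysis plan that is not shown. That is fair for what the article leaves open, but 2.16 does name the between-arm tests, and those named lack a baseline term.

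Finally, the envelopes are already filled and 2.1 puts the start at February 2023, before publication. Changing the allocation now would ordinarily need ethics review and cannot rebalance patients already allocated. This is why the point rests on the analysis and not on the envelopes.

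**Conclusion.** The point holds as a worthwhile improvement to the analysis, not as an error in the randomisation. Overall type I error is valid. The roughly 6–20% chance of a 20-point gap depends on borrowing a 20–50% prevalence for the trial's baseline; a flat 10–20% would be too strong, since it fits a fixed 30/30 split with an even number of cases, and section 3 leaves open that dumping may be rare. The conditional error and power figures rest on assumed effects of 0.75–1.5 SD, and the harm shrinks with the effect.

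The case for adjusting does not need an unlucky allocation: on the same assumptions, it lifts power from about 86% to 89–99% on average. Body weight and BMI, also main outcomes, are affected only as far as baseline dumping predicts them.

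**What to change.** In 2.16, replace the unadjusted between-arm tests of the Sigstad and Arts scores with a baseline-adjusted ANCOVA or mixed model: week-3 and week-6 score on arm, with the baseline score or baseline dumping status as covariate. State which covariate is used before allocation is revealed to the analyst. The cost is about one sentence and one degree of freedom; the data are already collected under 2.12.

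Optionally, for patients not yet randomised, use separate envelope sets by baseline dumping status in permuted blocks. This mainly balances the dumping-status subgroup. It costs re-preparing unused envelopes, an amendment with ethics review, scoring the Sigstad questionnaire before the envelope is opened, and possibly arms a patient or two away from 30/30. If enrolment is well advanced, the model term alone is enough.

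### Handing over a random envelope leaves the generated sequence unused and its order unverifiable, and simple 1:1 randomisation does not assure the stated 30 per arm

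*Protocol article*

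**What the plan says.** Protocol article, section 2.7, on the list: "a 1:1 simple computer-based random number table without stratification was generated via IBM SPSS statistics version 22". The sequence number for each allocation, together with the matching point picture and name, "was placed inside 60 nontransparent, sealed envelopes". No number on the outside of an envelope is mentioned.

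The same section, on issue: "At the time of intervention, a study research assistant will deliver a random envelope to the acupuncture doctor". Then: "The acupuncture doctor will attach the patient’s information to the envelope", and the doctor treats according to what the envelope contains. The text does not say whether the patient's details are attached before or after opening.

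Section 2.2, on arm sizes: "The patients will be randomly divided equally into 30 patients in the intervention or the control group", once eligibility is met and consent obtained. The abstract and section 2.14 also give 30 per group, and section 2.1 gives a 1:1 ratio. Blocking or a list with fixed totals is not mentioned anywhere.

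**The concern.** There are two separate problems in the allocation procedure as published.

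The first is the link between sequence and patient. A generated sequence protects against selection when patient *k* receives entry *k* and this can be shown afterwards. If any envelope may be taken from the stock, the sequence no longer fixes the assignment. With the number inside, nothing on the outside shows which envelope is due next, so a skipped or exchanged envelope would leave no gap in a visible order. The person who opens it must learn the arm in order to treat. If the patient is not recorded first, an opened envelope could be put back and replaced. This is a single-centre trial with an unblinded acupuncturist, so sound allocation is one of its main safeguards.

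The second is the description of the list. Simple randomisation lets the arm sizes vary by chance, yet the article states the sizes as fixed.

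**Working it through.** **1. The plan's own figure.** Inputs from section 2.14: two-tailed *t* test, effect size *d* = 0.8, power 80%, drop-out 15%. The 5% significance level is from section 2.16. The noncentral *t* calculation gives 26 per arm, 52 in total, with power 0.807. Inflating by multiplication gives 52 × 1.15 = 59.8, so 60; dividing gives 52 / 0.85 = 61.2, so 62 with equal arms. The stated total of 60 is therefore reproduced by the multiplication route. (Section 2.14 calls 26 a total; that is a separate matter.)

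**2. Arm sizes under simple 1:1 randomisation.** If each of 60 assignments is an independent fair draw, the size of one arm is Binomial(60, 0.5).

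- P(exactly 30:30) = C(60,30) / 2^60 = 0.103, so P(unequal) = 1 − 0.103 = 0.897.
- The 2.5% and 97.5% points for one arm are 22 and 38.

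| Split at least as unequal as | Probability |
|---|---|
| 26:34 | 0.366 |
| 24:36 | 0.155 |
| 22:38 | 0.052 |

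**3. Arm sizes under a restricted list.** If the 60 envelopes hold 30 of each allocation and all are used, P(30:30) = 1. This is true whether they are used in order or drawn blindly. If recruitment stops early, even this list does not guarantee equal arms.

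**4. Effect on power.** For a two-sample *t* test the noncentrality is *d* × √(n₁n₂/(n₁+n₂)).

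| Split | n₁n₂/60 | Power at *d* = 0.8, no drop-out |
|---|---|---|
| 30:30 | 15.0 | 0.861 |
| 26:34 | 14.7 | 0.855 |
| 24:36 | 14.4 | 0.847 |
| 22:38 | 13.9 | 0.836 |

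At 22:38 the information is 13.93 / 15 = 0.93 of that at 30:30. Drop-out lowers all four power values, but if it is the same proportion in both arms this ratio does not change.

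**5. The envelope step.** No arithmetic applies. The text supports three statements: the sequence number is inside; the envelope handed over is described as random, not as the next in sequence; and the acupuncture doctor attaches the patient's details at an unstated moment. It follows that the sequence does not determine the assignment and that use in order cannot be shown. It does not follow that anyone knew or chose an allocation. The documents give no basis for sizing a selection bias.

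**The case against.** A reader might go further in four ways, and on each the other side has a good answer.

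- *The assistant chooses the arm.* The documents do not support this. The envelopes are opaque and sealed with the contents inside, and nothing gives the assistant knowledge of them. A blind draw from a fixed 30/30 stock is itself a valid random permutation. The wording may also be a loose way of saying randomisation envelope. What stands is that the published procedure relies on the draw being blind and does not provide the means to show it.
- *Nothing can be audited.* Too strong. The doctor attaches the patient's details to an envelope that contains the sequence number, so patient, number and allocation can be linked. Order of use, and recording before opening, cannot be shown.
- *Equal arms are impossible.* Wrong. A 30:30 split has probability 0.103 under simple randomisation and is certain if 30 + 30 envelopes are all used. Sixty envelopes filled in advance make that reading plausible, with *simple* perhaps meaning unstratified and unblocked. The article does not say what the envelopes hold, so neither reading can be confirmed.
- *The trial loses its power.* It does not. Even at 22:38 the power without drop-out is 0.836.

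It can also be said that logs and issuing instructions belong in the full protocol, and that section 2.2 already places randomisation after eligibility and consent. Both are fair. But section 2.7 does set out the procedure, and the point concerns what it states: random issue, and a simple list alongside fixed equal arms.

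**Conclusion.** The point holds in two limited parts.

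First, as section 2.7 is worded, the generated sequence does not decide who receives which arm, the order of use cannot be verified, and recording of the patient before opening is not stated. The step is open to selection. Bias is not shown and cannot be sized, and a truly blind draw would still be chance-based.

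Second, "a 1:1 simple computer-based random number table without stratification was generated" and exactly 30 per arm do not fit together as worded. If the list really is simple, the stated sizes are missed with probability 0.897. If it holds 30 of each, the label is wrong. The probabilities assume independent fair assignment of all 60 patients; the power values assume *d* = 0.8, a two-sided 5% level and no drop-out. Under either reading the effect on power is small, so the consequence is for the integrity and correct reporting of the allocation. The sponsor should correct it.

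**What to change.** - Number the envelopes on the outside and issue them in strict numerical order, after consent and eligibility are confirmed.
- Write the patient identifier and date on the sealed envelope and in a log before it is opened.
- Section 2.1 gives February 2023 as the start, so some envelopes may already have been used. Reconcile these against the generated list and document any departure from its order.
- Describe the list as what it is (a fixed 30/30 random permutation, or permuted blocks if those were used). If it was truly simple, drop the statement of exactly 30 per arm in the abstract and sections 2.2 and 2.14.

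The cost is a log sheet, an instruction to the research assistant and the acupuncture doctor, and a few changed sentences. The sample size does not change. The envelopes already prepared can stay in use if they still match the list and are numbered outside, which the person who prepared them could do from the list without opening them only if they were kept in order; otherwise the unused ones need to be prepared again.
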